A confirmatory ELISA will be performed for all 10-month follow-up tests that are positive or in question. The samples will be sent to Tulane University. Serologic analysis will be performed according to the manufacturer protocol using the FDA-cleared Hemagen Chagas Kit (Hemagen Diagnostics, Inc., Columbia, Maryland), a qualitative ELISA designed for the detection of circulating antibodies to *T. cruzi* in serum and plasma.

Congenital infection with *T. cruzi* is sought for by direct microscopic examination of blood buffy coat collected in six centrifuged microhematocrit heparinized tubes as previously described [2,14,38,39]. In those cases in which it is not possible to collect enough blood to fill 6 capillary tubes, collecting blood to fill at least one capillary tube will be considered acceptable. The detection limit of such parasitological detection was estimated to be 40 parasites/ml (p/ml) [38,39], which allowed the detection of more than 90% of the congenital cases in Bolivian endemic areas [40]. The number of positive microhematocrit tubes containing parasites, as well as the number of detected parasites per tube, allowed estimation of parasitemia as either low (≥ 40 p/ml - < 150 p/ml), medium (≥ 150 p/ml - ≤ 400 p/ml), or high (> 400 p/ml). Positive parasitological examinations will be filmed when possible. The films will be downloaded to the Chagas study webpage and shared between the study sites.

We will perform molecular tests to estimate the parasitic DNA amount (PCR followed by a qPCR in positive cases) and to identify the *T. cruzi* genotype (TcI and/or Non-TcI) on the blood of infected mothers. We will also perform PCR followed by genotyping on the umbilical cord blood samples. An international consensus has recognized direct parasitological examinations of cord or neonatal blood collected in capillary tubes, as well as serological investigations of infant blood at 10 months of age, as the best tools for the biological diagnosis of *T. cruzi* congenital infection, whereas PCR must still be standardized and validated for such use [2]. Thus, the research team is using blood parasitological examinations and late serology to identify infected newborns. PCR will not be used for diagnostic purposes, but it will aid in verifying the presence of parasitic DNA in samples before they are quantified via qPCR or before genotyping.

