### Sample size

We are planning to study 600 mothers with *T. cruzi* infection. The sample size will be achieved by recruiting 13,000 women in Mexico (estimated seroprevalence of 1% in Merida and 0.4% in Valladolid), 7,500 in Honduras (estimated seroprevalence of 4%), and 10,000 in Argentina (estimated seroprevalence of 2%). Based on our pilot study, we estimate that 20% of deliveries will be excluded because the age of the mother will be <18 or because consent is not obtained. In addition, we estimate that 5% of the women will be ineligible because they live outside of the follow-up area in Mexico (which includes the entire Yucatan Peninsula) and that 10% will live outside of the follow-up areas in Honduras and Argentina (which include only each hospital’s department or province).

We estimate that we will recruit 300 mothers with TcI infection and 300 mothers with Non-TcI infection. We will have more than 80% power to detect a difference of 1% transmission for TcI versus 5% for Non-TcI. We estimate that the loss to follow-up will be lower than 10%.

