### Analysis plan

We will compute the rate of congenital transmission among seropositive mothers according to the exposure to TcI or Non-TcI with the corresponding confidence intervals and compare them using binomial exact tests. A seropositive mother will have at least one positive rapid test on cord blood and a positive ELISA on maternal blood. Cases with TcI/Non-TcI co-infection and with maternal HIV/AIDS will be analyzed separately, and transmission rates will be compared to the rest of the population.

In a second step, we will repeat the analysis after excluding infants with negative parasitological examinations and negative PCR on cord blood, and with a history of transfusion and/or organ transplant, and/or who are living in households exposed to the vector (presence of vectors and/or location in an area at risk of vector transmission). The resulting congenital transmission rate will be a more conservative estimate, which will be less likely to be biased by non-congenital routes of transmission. We will also stratify according to breastfeeding (yes/no), another potential route of neonatal transmission.

We will adjust the comparison of TcI/Non-TcI transmission rates for potential confounders:

– Maternal age at delivery (in five-year categories);

– Parity (primiparae/multiparae);

– Presence of vectors in the household (yes/no);

– Maternal parasitic DNA amount;

– Mode of delivery (C. section vs. vaginal); and

– Infected sibling (yes/no) (siblings previously treated for *T. cruzi* infection will be presumed as having been infected).

Mantel-Haenszel chi-square tests will be used for stratified analyses, which will take one categorical factor into account at a time. A logistic regression will be also performed and will include all potential confounders. Adjusted odds ratios (OR) and confidence intervals will be estimated.

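### The second-step exclusion, read literally, drops exposed uninfected infants but keeps exposed early-positive cases, so the resulting rate is not assured to be conservative

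*Protocol article*

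**What the plan says.** The Analysis plan of the protocol article sets the base analysis: "We will compute the rate of congenital transmission among seropositive mothers according to the exposure to TcI or Non-TcI". Its denominator therefore contains infected and uninfected infants of seropositive mothers.

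The second step follows: "we will repeat the analysis after excluding infants with negative parasitological examinations and negative PCR on cord blood, and with a history of transfusion". Organ transplant is listed beside transfusion as a further alternative, and the last alternative in the list covers infants "who are living in households exposed to the vector (presence of vectors and/or location in an area at risk of vector transmission". Of this step the plan claims: "The resulting congenital transmission rate will be a more conservative estimate, which will be less likely to be biased by non-congenital routes of transmission".

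Three other places bear on the point:

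- **Variables.** An infant is a case on any of three criteria: parasites in cord blood, parasites at 4–8 weeks, or antibodies persisting at 10 months. Births without a genotype count as TcI in Mexico and Honduras and as Non-TcI in Argentina.
- **Entomological data.** The estimate is 100 seropositive households in Mexico, 300 in Honduras and 200 in Argentina. House infestation is expected to be limited in Argentina and Honduras, and collections are expected to be much larger in Mexico. No exposed share is given for any country.
- **Blood samples and laboratory evaluations.** Microscopy is said to have found more than 90% of congenital cases in Bolivian endemic areas.

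**The concern.** The second step is the plan's check that cases found only by 10-month serology were not acquired after birth. For that purpose, the infants in doubt are infected infants with no early evidence and another possible route of infection.

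The rule is not limited to them. An uninfected infant is negative on microscopy and, apart from false positives, on cord PCR. Among exposed infants, the early-test condition is therefore met by almost every non-case and by few cases. Exclusion depends on tests that partly define the outcome, and it works mainly on the denominator.

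Two things are at stake. The rate may be reported as conservative when it has been pushed up. And if the exposed share differs between the TcI and Non-TcI groups, the push differs too, so the check can create or hide part of the difference that the study is meant to measure.

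**Working it through.** **The plan's own figures.** The plan gives no figure for the second step. Its nearby power statement, "We will have more than 80% power to detect a difference of 1% transmission for TcI versus 5% for Non-TcI" with 300 per group, comes to 82.1% by the normal approximation (two-sided 5% assumed; 79.8% by Fisher's exact test). It concerns the primary comparison and is not affected here.

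**Inputs**

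- p, true congenital rate: 5%, the plan's Non-TcI design value; 3% as a variant.
- s, share of congenital cases positive on an early test: 0.9 assumed, anchored on the plan's microscopy figure; range 0.5 to 1.0.
- e, share of infants exposed: not in the documents; assumed values shown.
- Exposure is assumed independent of congenital infection. No uninfected infant is assumed PCR-positive unless stated.

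**Formula under the literal reading.** Per infant enrolled:

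- cases kept = p(1−e) + p·e·s
- all infants kept = (1−e) + p·e·s
- step-two rate = [p(1−e) + p·e·s] / [(1−e) + p·e·s]

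Subtracting p gives p·e·s·(1−p) / [(1−e) + p·e·s]. This is positive whenever e and s exceed zero, so only the size depends on the assumed values.

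**Size.** At p = 5%, s = 0.9, e = 50%: (0.025 + 0.0225) / (0.5 + 0.0225) = 0.0475 / 0.5225 = 9.09%.

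| e | step-two rate (true 5%) |
|---|---|
| 10% | 5.47% |
| 30% | 6.80% |
| 50% | 9.09% |

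At e = 50%, moving s from 0.5 to 1.0 gives 7.32% to 9.52%. If 10% of uninfected exposed infants were cord-PCR-positive and so kept, 9.09% would fall to 8.33%.

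**Against step one.** Let q be the proportion of otherwise uninfected exposed infants infected after birth, all early-negative. Step one gives p + (1−p)·e·q. With p = 5%, e = 50%, s = 0.9:

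| q | step one | step two |
|---|---|---|
| 0 | 5.00% | 9.09% |
| 5% | 7.38% | 9.09% |
| 10% | 9.75% | 9.09% |

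The two are equal at q = (0.0909 − 0.05) / 0.475 = about 8.6%.

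**Between groups.** Use the plan's country mix with default assignment (100 Mexican and 300 Honduran households as TcI), and assume 10% exposed in Honduras and Argentina.

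- Mexico 70%: TcI e = (70 + 30)/400 = 25%. At a true 5% in both groups, the rates are 6.40% versus 5.47%, ratio 1.17.
- Mexico 100%: TcI e = (100 + 30)/400 = 32.5%. At a true 3% in both groups, (0.02025 + 0.008775) / (0.675 + 0.008775) = 4.24% versus 3.29%, ratio 1.29.

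Both true ratios are 1.

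**Alternatives at p = 5%, s = 0.9, e = 50%.** Keeping everyone and recoding only exposed, early-negative cases gives 0.0475/1 = 4.75%. Dropping all exposed infants gives 5.00%. The literal rule gives 9.09%.

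**The case against.** **The sentence can be read otherwise.** The vector clause can attach directly to infants, so that vector exposure alone excludes. Exposed cases with positive early tests then leave too, and the vector inflation does not arise. The sentence may also be shorthand for infected infants without early evidence, which its stated purpose would suit. This stands: a reader might infer that every reading inflates the rate, and the documents do not support that. Nor do they support taking the criteria as separate grounds for exclusion, which would remove nearly all uninfected infants and send the rate towards 100%; no one is likely to have meant that. But the literal conjunction is a natural reading, and an analyst could follow it.

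**Conservative may mean lower than step one.** On that measure the rule can succeed when postnatal infection is common, as the 10% row shows. This also stands, but success then depends on an unknown quantity, and the rate still exceeds the true congenital rate.

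**The group distortion is not quantified by the documents.** A reader might infer a large spurious ratio, for example 1.7 from 50% versus 10% exposed. No exposed share is given, and Mexico is only 100 of the 400 default TcI households, so high exposure there is diluted. A larger ratio would need high exposure in Honduras too, which the at-risk-area criterion might produce but the plan does not quantify.

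**It is a secondary analysis, and confounders are adjusted for elsewhere.** The first part is right and limits the severity. The adjustment does not settle the matter: its vector covariate is presence in the household, whereas the exclusion also uses location, and the plan does not say that the second step is adjusted.

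**Conclusion.** The point holds for the literal reading and should be fixed. Under that reading the step-two rate exceeds the true congenital rate for any exposed share above zero, apart from dampening by false-positive PCR. With 90% of cases positive early and a true rate of 5%, it is 5.5% at 10% exposed, 6.8% at 30% and 9.1% at 50%. It is therefore not assured to be more conservative than step one.

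If exposure differs between groups, as the plan's expectation for Mexico suggests, the TcI versus Non-TcI comparison is distorted by an unknown amount. The ratio is about 1.2 to 1.3 with the plan's country mix, 10% assumed exposure in Honduras and Argentina, and 70% to 100% in Mexico; it is more if at-risk-area exposure in Honduras is high.

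The direction follows from the rule; the sizes rest on assumed exposure and early-positive shares. The primary rate, the primary comparison and the power statement are untouched, so this is a should-fix and not a threat to the main result.

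**What to change.** Rewrite the exclusion sentence as one rule. Either of these is sound:

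1. **Recode, preferred.** Keep every infant in the denominator. Count as not proven congenital only those infected infants with negative parasitological examinations and negative cord PCR who also had a transfusion, a transplant or vector exposure. This lowers the rate slightly (4.95% at 10% exposed and 4.75% at 50%, for a true 5%), so it is conservative.
2. **Restrict.** Exclude all infants with any of these exposures, whatever their test results. This leaves the congenital rate unbiased if exposure is unrelated to congenital infection. The cost is sample size: at 50% exposed, 300 infants in a group become 150.

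Under option 1, state also whether the 4–8-week examination counts among the parasitological examinations or only the cord examination; the present wording leaves this open.

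The cost is one reworded sentence, made before the data are analysed. No new data are needed.

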### Study population

Participating sites include: Hospital Materno Infantil and Hospital General Valladolid, both in Yucatán, México; Hospital Enrique Aguilar Cerrato, La Esperanza in Intibucá, Honduras; Hospital Santa Bárbara in Santa Bárbara, Honduras; and Instituto Maternidad Provincial Nuestra Señora de las Mercedes in Tucumán, Argentina.

All consecutive live births occurring during the defined study period will be included, irrespective of the gestational age or the route of delivery (vaginal or cesarean).

All subjects must meet all of the inclusion criteria to participate in this study.

• *Inclusion criteria***:** Women 18 years old or more, informed consent, live birth.

All subjects meeting any of the exclusion criteria at baseline will be excluded from study participation.

• *Exclusion criteria***:** Women residing outside of the follow-up area.

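### The logistic regression with all six confounders needs about 9 to 11 coefficients, but the planning rates give only 14 to 18 infected infants to estimate them.

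*Protocol article*

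**What the plan says.** The Analysis plan first compares TcI and Non-TcI transmission rates, unadjusted, by exact tests. It then adjusts for six potential confounders: age, parity, household vectors, parasitic DNA, mode of delivery and infected sibling. Age is listed as "Maternal age at delivery (in five-year categories"; parasitic DNA appears only as "Maternal parasitic DNA amount", with no functional form. Mantel-Haenszel tests handle one factor at a time. For simultaneous adjustment the text is definite: "A logistic regression will be also performed and will include all potential confounders". Adjusted odds ratios with confidence intervals are promised.

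The Sample size section plans 300 TcI and 300 Non-TcI mothers, with more than 80% power "to detect a difference of 1% transmission for TcI versus 5% for Non-TcI", and loss to follow-up below 10%. The Entomological data section gives different numbers of seropositive households: 100 in Mexico, 300 in Honduras and 200 in Argentina. Under the default strain assignment by country, that is 400 TcI and 200 Non-TcI.

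**The concern.** Strain is close to a proxy for country, because births without a successful genotype are assigned by country (Variables section). Confounding between countries is therefore the main threat to Aim 1, and this regression is the only analysis that controls several factors at once. If the model is too large for the number of infections, some categories will contain no infected infant and their coefficients will have no finite estimate. The strain odds ratio may then be distorted or, occasionally, not exist. The number of events follows from the plan's own rates, so the mismatch can be seen before any data are collected.

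**Working it through.** **1. The plan's power figure.** With 300 per group, 1% vs 5%, and two-sided alpha 0.05 (assumed; not stated), the mean rate is 0.03 and

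z = [0.04·√300 − 1.96·√(2·0.03·0.97)] / √(0.01·0.99 + 0.05·0.95) = (0.6928 − 0.4728)/0.2396 = 0.918,

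so power is 82.1%. Full enumeration of Fisher's exact test gives 79.8%. The stated figure reproduces to within the choice of test, so these are the right planning inputs.

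**2. Expected infections.**
- 300/300: 300·0.01 + 300·0.05 = 3 + 15 = 18.
- 400/200: 400·0.01 + 200·0.05 = 4 + 10 = 14.
- With 10% loss: 16.2 and 12.6.

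**3. Coefficients, excluding the intercept.** Strain, parity, vectors, parasitic DNA (if linear), mode of delivery and infected sibling take 6. Enrolment starts at 18 ("Women 18 years old or more, informed consent, live birth"). Six bands (18–19, 20–24, and so on to 40+) add 5, total 11; four bands add 3, total 9. The number of bands is an assumption.

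**4. Events per coefficient.** 14/11 = 1.3; 18/11 = 1.6; 14/9 = 1.6; 18/9 = 2.0. After 10% loss with 11 coefficients: 12.6/11 = 1.1 and 16.2/11 = 1.5. At 300/300 with TcI at 1%, the Argentine range quoted in the Background gives:
- Non-TcI 2.6%: 3 + 7.8 = 10.8 events, 10.8/11 = 1.0.
- Non-TcI 7.9%: 3 + 23.7 = 26.7 events, 26.7/11 = 2.4.

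**5. Separation of any coefficient.** There were 600 simulated trials per cell at 1% vs 5%. All covariate prevalences are assumed, and covariates are independent of strain.

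| Assumed covariates | 300/300 | 400/200 | 270/270 | 360/180 |
|---|---|---|---|---|
| Sparse: six bands, oldest 2%; vectors 5%; infected sibling 4% | 93% | 95% | 94% | 97% |
| Middling: six bands, oldest 4%; vectors 15%; sibling 10% | 74% | 83% | 81% | 87% |
| Favourable: six near-equal bands; vectors 30%; sibling 25% | 30% | 49% | 40% | 56% |
| Favourable, four equal bands | 11% | 19% | 15% | 24% |

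With middling prevalences at 300/300, separation was 93% at Non-TcI 2.6% and 52% at 7.9%.

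**6. Separation of the strain coefficient.** This occurred in 1% to 9% of trials across the cells above. It arises mainly when no TcI infant is infected: 0.99^300 = 4.9%, 0.99^400 = 1.8%; after 10% loss, 0.99^270 = 6.6% and 0.99^360 = 2.7%.

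**7. Bias and coverage of finite fits.** The true odds ratio is (0.01/0.99)/(0.05/0.95) = 0.19, log −1.65. After event-free levels were dropped, maximum likelihood gave a usable fit in 450 to 569 of 600 trials. Among those, mean log odds ratio bias was −0.07 to −0.16, which is 4% to 10% of 1.65, and Wald coverage was 95.5% to 98%.

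**8. Imprecision before adjustment.** With 3/300 and 15/300, the standard error of the log odds ratio is √(1/3 + 1/297 + 1/15 + 1/285) = 0.64. The 95% interval runs from about 0.055 to 0.67. Adjustment does not cure this.

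**9. Firth fit of the same full model.** The strain estimate was finite in 599 or 600 of 600 trials, mean bias was within about 0.06, and Wald coverage was 93% to 95%.

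**The case against.** A reader might infer from the event counts that separation is near certain and the adjusted odds ratio and interval are worthless. The article does not support that:
- It gives neither covariate prevalences nor the number of age bands, and the simulated rate runs from 11% to 97%.
- Most separation falls in an age, sibling or vector category. That does not make the strain odds ratio infinite.
- Finite strain estimates had modest bias and conservative coverage.
- Dropping mothers in an event-free category is not a separate loss. Once that category's coefficient diverges, those mothers carry no information on the other coefficients.

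It is also fair to say that the estimator and coding are not spelled out, that a condensed article may leave them to a fuller document, and that the regression supplements an exact comparison and stratified tests. An ordered age score would need only 7 coefficients, or 14/7 = 2.0 to 18/7 = 2.6 events each.

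All of this stands and limits the size of the point. It does not remove it. The instruction to put every listed confounder in one logistic model, with categorised age, is stated rather than omitted, and no reading of the coding gives a comfortable number of events.

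Three features could make the fit worse than simulated. Vector collections are expected to be larger in Mexico, so that covariate is tied to strain. Infected sibling is in practice confined to multiparae. Quantitative PCR is run only on PCR-positive samples, so DNA amount in the other mothers needs a coding rule.

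**Conclusion.** The concern holds in a limited form. At the planning rates the stated model has about 1.3 to 2 events per coefficient, with 3 or 4 events in the whole TcI group. Under standard maximum likelihood, some coefficient is likely to separate if covariates are sparse or middling, and may well not if they are common and age bands are few. The strain odds ratio is inestimable in about 1% to 9% of trials; otherwise it is imprecise and about 0.1 too far from 0 on the log scale.

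This rests on 1% vs 5% transmission, 9 to 11 coefficients, assumed prevalences, covariates independent of strain, and logistic regression meaning ordinary maximum likelihood. The unadjusted exact comparison is untouched.

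A reader might also infer that confounders should be cut to fit the events. The evidence does not show that: the Background itself cites parasitic load and family clustering as relevant to transmission, and Firth estimation behaved acceptably with the full set.

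**What to change.** State in the Analysis plan that the adjusted TcI/Non-TcI odds ratio will be estimated by Firth penalised-likelihood logistic regression with profile-likelihood intervals, or by exact logistic regression. Enter age as one linear or ordered term instead of five-year indicators. Keep the listed confounders, including parasitic DNA and infected sibling, unless the sponsor justifies a smaller set before the data are seen. Reconcile the 300/300 and 400/200 splits so that the expected number of events is clear.

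The cost is a wording change, slightly coarser age control, and a routine other than standard logistic regression. The sponsor should confirm that the named Stata release offers it. The simulated Firth coverage used Wald intervals, so the profile-likelihood choice was not itself tested. No estimator removes the imprecision that comes from 3 or 4 TcI events.

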– Gestational age (completed weeks), based on the Last Menstrual Period (LMP) or a clinical estimate (including ultrasound, if available) [16]. In the absence of an ultrasound, the clinical estimate will be based on the Capurro Score [17]. This score is the standard method to evaluate gestational age by physical examination of an infant at birth in Argentina and is widely used in Latin America. The clinical estimate will be used if the discrepancy between the LMP-based estimate and the clinical estimate is greater than 10 days; a preterm birth is <37 weeks;

– Birthweight (grams); a low birthweight baby weighs <2,500 g;

– Head circumference (cm);

– Length (cm);

– Neonatal complications: We will use the definitions of Torrico et al. [14] for the following variables, to be registered at a physical examination of the infant at not later than 24 hours of life:

– Hepatomegaly (when ≥ 2 cm below the right costal margin);

– Splenomegaly (whatever the spleen size under the left costal margin);

– Anasarca (palpebral, genital, or leg edema alone will not be considered);

– Petechiae (whatever their localization);

– Respiratory Distress Syndrome (RDS) will be considered when at least one of the following signs is present: tachypnea, throbbing of the ala nasi, expiratory grunting, intercostal retraction, facial or systemic cyanosis (peripheral cyanosis will not be considered);

– Neurological signs will be classified as present or absent based on tone, level of alertness, Moro and other primary neonatal reflexes, deep tendon reflexes, spontaneous motor activity, pupil diameter (in search of mydriasis or miosis), bulging of fontanelles, and convulsions.

Data about birthweight of siblings and breastfeeding are collected by interviewing the mother at home using the Honduras Demographic and Health Survey (DHS) questions [18]. The DHS is a standardized survey administered around the world, and it includes validated questions and allows for international comparisons [19]. For each newborn and his/her siblings, we will also collect data about blood transfusions, organ transplants, and previous screening and treatment for *T. cruzi*.

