### Entomological data

Entomological data will be obtained from two different sources to estimate vectorial exposure in the households from seropositive mothers. First, we will use vector distribution and house infestation data from the respective vector surveillance and control programs in Argentina and Honduras, which provide geocoded information and maps on the presence of vectors of different species at the village/locality level. For each household of a seropositive mother, we will thus determine if it is located in a village with or without known house infestation by triatomines using cumulated vector data from the past five years. For the Yucatan Peninsula, Mexico, in the absence of vector control programs, we will use published entomologic risk maps [22]. Based on these maps, households located in villages with low or absent risk will be classified as without house infestation, and households from villages with medium or high risk will be classified as with house infestation.

Second, we will use the community participation method, which was successfully piloted in and previously used in Argentina as well [23]. All of the households from seropositive mothers will be included, corresponding to an estimated 100 households in Mexico, 300 in Honduras, and 200 in Argentina. During the first household visit, information on Chagas’ disease and triatomines will be provided, including photographs and the display of dried specimens of the vector, to ensure that study participants will recognize the vector. Participants will then be instructed to collect any triatomines observed inside (domestic) or outside (peri-domestic) of their homes using a safe procedure and to place them into separate labeled plastic vials or bags. Any insects captured since the time of the initial visit will be gathered during the second visit at 10 months. Triatomine species will be identified by local entomologists from vector control programs in Argentina and Honduras and by entomologist researchers in Mexico, using established entomological keys [24,25].

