We will describe birth outcomes (PROM, gestational age, birthweight, head circumference, length, and neonatal complications) of infected and uninfected infants by calculating proportions and confidence intervals for categorical variables (including preterm birth and low birthweight) and means and standard deviations for continuous ones. In a next step, we will stratify the analysis by DTU (TcI/Non-TcI). We will compare intrauterine growth restriction (IUGR) rates. A newborn will be classified as IUGR if its birthweight is below the tenth percentile of the sex-specific birthweight for gestational age curves proposed by Williams et al. [42] for single and multiple births. These growth curves are recommended by the WHO as reference patterns for international comparisons [43,44]. We will use the same reference for the three countries to allow for comparison among sites. In addition, we will also compute IUGR rates according to a more recent U.S. reference curve [45] for single live births to facilitate comparisons with the U.S. literature. We will also analyze birthweight data of infected and uninfected siblings by calculating proportions of low birthweight and “very small babies” and confidence intervals, mean birthweights, and standard deviations.

We will use STATA Version 8.0 [46] software for data analysis.

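### The plan compares fetal growth only as IUGR yes/no; a gestation-adjusted comparison on the full birthweight scale beside it would recover information, by an amount that depends on assumptions the protocol does not state

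*Protocol article*

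**What the plan says.** Aim 3 (Background) is to describe birth outcomes by infection status and DTU. The Analysis plan gives proportions with confidence intervals for categorical outcomes and means with standard deviations for continuous ones, first by infection status and then stratified by DTU. It then adds: "We will compare intrauterine growth restriction (IUGR) rates". The definition follows: "A newborn will be classified as IUGR if its birthweight is below the tenth percentile of the sex-specific birthweight for gestational age curves". The rates are to be computed on a WHO-recommended curve and again on a U.S. curve, and the reasons given are comparability between sites, internationally and with the U.S. literature.

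Among the infant birth outcomes, IUGR is the only one that the plan says it will compare. The sentence names neither the groups nor the test.

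The Variables section records birthweight in grams alongside a low-birthweight category ("Birthweight (grams); a low birthweight baby weighs <2,500 g"), gestational age in completed weeks, and multiple births. Infant sex must also be available, because the curves are sex-specific.

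**The concern.** A tenth-percentile cut treats every infant above it as alike and every infant below it as alike. If infection or DTU shifts growth across the whole distribution, most of the evidence lies in infants who do not cross the line.

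The planned means do not fill this gap. A lower mean birthweight in one group can come from earlier delivery, slower growth or both. The Background itself cites an association of congenital infection with preterm birth, so the two are likely to be mixed. IUGR is the only planned summary that takes gestation into account.

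Comparability justifies the choice of reference curve and the reporting of IUGR rates. It is not a reason to have no full-scale comparison within the study. What is at stake is that a real difference in growth could be read as similar IUGR rates when data already collected would describe it more precisely.

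**Working it through.** **The plan's own power figure.** The only one is for Aim 1: "We will have more than 80% power to detect a difference of 1% transmission for TcI versus 5% for Non-TcI", with "We estimate that we will recruit 300 mothers with TcI infection and 300 mothers with Non-TcI infection". By the normal formula at a two-sided 5% level (assumed; the protocol states none), with mean rate 0.03:

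z = [0.04·√300 − 1.96·√(2·0.03·0.97)] / √(0.01·0.99 + 0.05·0.95) = (0.693 − 0.473)/0.240 = 0.92, so power is 82.1%.

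Fisher's exact test gives 79.8%. The stated figure is reproduced. No power is stated for IUGR.

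**Group sizes.** The Sample size section expects losses below 10%; taking 10% leaves 270 per DTU.
- Infected infants: 0.01·270 + 0.05·270 = 2.7 + 13.5 = 16.2, about 16.
- Uninfected infants: 540 − 16 = 524.
- IUGR is known at birth, so 300 versus 300 is also relevant for the DTU contrast; it is used below as a sensitivity check.

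**Assumptions not in the protocol.** IUGR rate 10% in the reference group; size for gestation normal with equal SD; a shift of d SD in the other group; two-sided 5%; contrasts by infection status and by DTU.

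**Formulas.**
- Full scale: two-sample t test, noncentrality d/√(1/n₁ + 1/n₂), n₁ + n₂ − 2 degrees of freedom.
- Cut: pooled two-proportion z test, with rate Φ(Φ⁻¹(0.10) + d) in the shifted group. For example, d = 0.5 gives Φ(−1.282 + 0.5) = 21.7%.

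**Infected versus uninfected, 16 versus 524**

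| d | Shifted IUGR rate | Full scale | IUGR yes/no | Loss (points) |
|---|---|---|---|---|
| 0.1 | 11.9% | 6.8% | 7.0% | about 0 |
| 0.2 | 14.0% | 12.3% | 11.4% | 1 |
| 0.3 | 16.3% | 21.9% | 17.5% | 4 |
| 0.5 | 21.7% | 50.3% | 35.3% | 15 |
| 0.7 | 28.0% | 78.6% | 57.9% | 21 |

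Expected IUGR cases among the 16 infected infants run from 16·0.10 = 1.6 (no shift) to 16·0.28 = 4.5 (d = 0.7).

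**TcI versus Non-TcI, 270 versus 270**

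| d | Full scale | IUGR yes/no | Loss (points) |
|---|---|---|---|
| 0.1 | 21.3% | 10.6% | 11 |
| 0.15 | 41.3% | 18.0% | 23 |
| 0.2 | 64.0% | 29.2% | 35 |
| 0.25 | 82.6% | 43.2% | 39 |
| 0.3 | 93.6% | 58.4% | 35 |
| 0.4 | 99.6% | 84.2% | 15 |
| 0.5 | 100% | 96.6% | 3 |
| 0.7 | 100% | 100% | 0 |

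**Sensitivity.**
- At 300 versus 300 (normal formula) the DTU losses are 12, 25, 39, 12 and 2 points at d = 0.1, 0.15, 0.25, 0.4 and 0.5: the same pattern.
- With Fisher's exact test the largest DTU loss is about 44 points.
- For reference rates of 5% to 20% and d = 0.1 to 0.5, the DTU loss runs from 0.5 to 52 points. The household counts in Entomological data ("corresponding to an estimated 100 households in Mexico, 300 in Honduras, and 200 in Argentina") imply 400 versus 200 by country; that raises the upper end to 54.
- For small shifts, the efficiency of a 10% cut is φ(1.282)²/(0.1·0.9) = 0.342. The cut therefore needs about 1/0.342 = 2.9 times the sample.

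**Standard errors with 16 infected infants.** Simulating no effect with 16 versus 524 and no covariates, the common robust (HC1) standard error rejects in about 7.4% of samples at a nominal 5%; with 18 versus 582 the figure is 7.1%. Uncorrected robust standard errors are therefore unsuitable for the infection contrast.

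**The case against.** The case against is substantial, and most of it limits the size of the point.

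- **Aim 3 is descriptive**, with no hypothesis and no power target. That stands, and power is used here only to express lost information. Even so, the plan goes beyond description when it commits to a comparison.
- **The groups are not named.** Infection status and DTU follow from the sentences just before, but a comparison between sites is also possible. The two contrasts are inferred.
- **IUGR is a recognised category**, and comparability is a sound reason to report it. That stands in full: the rates should stay.
- **Birthweight and gestational age are already summarised as means and SDs**, so a reader would see some of any difference. This is true but does not separate growth from gestation.
- **A continuous score could be left to a full analysis plan.** That is fair for its details. The point concerns a choice that the article does state.

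A reader might also infer a large loss whatever the true effect. The tables do not support that. For infection status the loss is negligible at small shifts, where neither analysis has useful power. For DTU it vanishes at large shifts, where both have ample power. Nor is the cut the main limit on the infection contrast: with about 16 infected infants, even the full-scale analysis reaches only 50% at d = 0.5.

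**Conclusion.** The point holds as a minor one. The plan's only gestation-adjusted growth comparison is a yes/no cut, and no full-scale counterpart is stated although the data for it are collected.

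The loss is conditional on a 10% reference rate, a normal shift with equal SD, a two-sided 5% level and inferred contrasts. It peaks at about 39 points for DTU at a shift of 0.25 SD and reaches about 21 points for infection status at 0.7 SD. Outside the middle of each range it is small or nil. Because the protocol fixes none of these inputs, no single loss figure can be attributed to it.

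It would be tempting to conclude that the plan is in error or that IUGR is the wrong measure. The documents support neither: no stated figure is wrong, and reporting IUGR serves the comparisons that the plan names.

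**What to change.** Keep the IUGR rates on both curves. Beside them, add a comparison of birthweight for gestation on its full scale, by infection status and, separately, by DTU, and name those groups. Either of these would serve:

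- a z-score from the reference curve; or
- a regression of birthweight on group, with gestational age modelled flexibly (not only as a straight line), infant sex and single or multiple birth.

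Report the mean difference with its confidence interval. For infection status, use ordinary model-based or small-sample-corrected standard errors, or a permutation test, and not uncorrected robust standard errors.

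The cost is a sentence or two in the Analysis plan and one extra analysis on data already collected. The result is not a clinical category, and a mean difference is less sensitive to a change confined to the lower tail. The retained IUGR rates cover both.
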